#### Early termination or dropout

2.8.7

##### Dropout criteria

2.8.7.1

1.If the patient is under prescription of the following medications that are expected to affect the safety and effectiveness of NBT and acupotomy, the medications cannot be taken from the time of screening until the completion of the study.① Concurrent use of medications that are prohibited for use with medications used for NBT.Medications that are likely to cause serious side effects in drug interaction studies.Medications whose mutual use is restricted with disodium dexamethasone injection: asunaprevir, daclatasvir, dronedarone hydrochloride, eliglustat, grazoprevir, ibrutinib, nilotinib hydrochloride monohydrate, olaparib, osimertinib, palbociclib, rilpivirine, rivaroxaban, ticagrelor, ceritinib, ribociclib, venetoclax, elbasvir, BCG strain, cobimetinib, cicletanine, etc. (Other medications used for NBT do not cause side effects of serious grade in drug interaction studies)② Strong opioid, local anesthetic administered by another physician than the one for this clinical studyHowever, anti-inflammatory analgesics and muscle relaxants prescribed for necessary causes at the discretion of the clinician can be administered^[13]^ (See rescue medications).③ Medications that may pose a risk to the patient or cause bias in the results as judged by the clinical investigator2.The patient requests to discontinue interventions or withdraws consent for participation3.The patient is judged to be unfit to continue in the study due to serious adverse reactions/medication reactions4.Serious protocol violations such as inclusion/exclusion criteria are newly discovered during the study5.Patients in the NBT and acupotomy combination treatment group who do not meet the criteria for early termination but have not conducted 6 or more of the 8 planned acupotomy treatments6.Patients who do not meet the criteria for early termination but fail to conduct even one of the planned NBT7.Patients who are judged to be unfit to continue in the study for other reasons at the discretion of the clinical investigator

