**Figure 1 F1:**
[figure not shown]
Study flow chart.

**Table 1 T1:** Clinical trial schedule and observation items.

Period		Screening^∗^ and Baseline	Treatment										Post Treatment	Early termination
Visit	Acupotomy + NBT group	Visit 1	Visit 2	Visit 3	Visit 4	Visit 5	Visit 6	Visit 7	Visit 8	Visit 9	Visit 10	Visit 11	Visit 12	Drop-out
	NBT group	Visit 1			Visit 2		Visit 3			Visit 4		Visit 5	Visit 6	
Day		0	1–3	4–6	7–8	9–11	12–14	15–17	18–20	21–22	23–25	26–28	56–58	
Written consent form		√												
Demographic survey		√												
Medical history, other medical history, and medication administration history		√												
Screening test^†^		√												
Selection/exclusion criteria		√												
Randomization (assignment of registration number)		√												
Physical examination and evaluation of vital signs		√	√	√	√	√	√	√	√	√	√	√	√	√
Medication administration history evaluation^‡^			√	√	√	√	√	√	√	√	√	√	√	√
Treatment	+ Acupotomy (combination treatment group)		√	√		√	√	√	√		√	√		
	NBT (all patients)				√					√				
Primary endpoint evaluation^§^		√					√					√	√	√
Secondary endpoint evaluation^||^		√					√					√	√	√
Exploratory efficacy evaluation^¶^													√	√^#^
Economic feasibility evaluation – cost evaluation^∗∗^		√					√					√	√	√
Adverse reaction monitoring			√	√	√	√	√	√	√	√	√	√	√	√
Economic feasibility evaluation – safety evaluation^††^			√	√	√	√	√	√	√	√	√	√	√	√

∗ One and 2 weeks are required from screening test to active treatment for combination treatment and NBT single treatment groups, respectively.

† Blood test [CBC 5 types, AST, ALT, ALP, albumin, BUN, protein, creatinine, total cholesterol, fasting glucose, RA, CRP, ASO, ESR, electrolyte 4 types (Na, K, Cl, T- CO_2_)]. It can replace test values performed within 8 weeks from screening.

‡ Concomitant medication history and adverse events monitoring are conducted at every visit for treatment and assessment.

§ ODI assessment.

|| Lower back and lower extremity pain (NRS) related to sacral neuropathy, quality of life (European Quality of Life 5 Dimension), Korean version of shortened MPQ, and Korean version of RMDQ.

¶ Additional NBT or surgical treatment within 4 weeks of the final procedure.

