# Exploratory evaluation is not conduced for patients who have completed treatment early. For patients who dropped out of the study, exploratory evaluation is conducted after 4 weeks from dropping out (exploratory effectiveness evaluation for dropout participants can be conducted through telephone counseling instead of in-person visits).

∗∗ Evaluation of direct non-healthcare, direct non-healthcare, and lost productivity costs.

†† Those patients who reported adverse reactions will complete EQ-5D by recalling time of adverse events.

Patients who undergo 1 NBT and show continued symptoms (patient's subjective pain improvement is less than 50% after the procedure or the numeric rating scale (NRS) score being 5 or higher) will undergo screening at 1 week after the first procedure. For screening, demographic information, medical history, physical examination, vital signs, questionnaire survey, laboratory test, and selection/exclusion criteria will be evaluated. Randomization and group allocation will be performed at screening and baseline. Fifty patients will be enrolled and randomly divided into 2 groups. Patients who are judged suitable for the study after the screening test and voluntarily agree to participate will be randomly assigned to either the NBT single treatment group (usual care group) or NBT + deeply inserted acupotomy treatment group in a 1:1 ratio (Fig. 1). Thereafter, the randomly assigned patients will undergo primary and secondary outcome evaluations and economic evaluation.

The NBT + deeply inserted acupotomy group will receive 8 acupotomy treatments (at visits 2, 3, 5, 6, 7, 8, 10, and 11) for 4 weeks as well as additional 2 NBTs (at visits 4 and 9) for 4 weeks. Then, the group will be followed-up for 4 weeks after the intervention treatment. The standard care group will undergo two NBTs (at visits 2 and 4) for 4 weeks and will be followed-up for 4 weeks after the intervention treatment. Primary and secondary outcomes, economic evaluation, and assessment of drug administration history will be conducted at visits 1, 6, and 11, and at the end of follow-up. To evaluate safety, evaluation of adverse events, vital signs, and economic feasibility will be conducted at every visit from visit 2 to visit 12. Laboratory tests will be conducted only at screening.

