### Recruitment, randomization, blinding, and nonblinding

2.6

Advertisements for patient recruitment will be posted on the Catholic Kwandong University, International St. Mary's Hospital's bulletin boards, along with posters, banner advertisements, and internet cafes. All advertisements will be run after institutional review board (IRB) approval.

Individuals who provide written consent to participate in the study will be assigned a screening number, according to the order of the outpatient visit at screening. Unblinded sub-investigators, who do not influence the research results and analysis, will refer to the randomization list that has been prepared by a commissioned professional statistician, and assign participation numbers. Participants will be allocated to the NBT group and the acupotomy + NBT group in a ratio of 1: 1. A block randomization table will be generated by an independent statistician and patients will be assigned to one of 2 groups according to the randomization table. Screening numbers, randomization numbers, and initials assigned to each participant will be used as subject identification codes to identify the participant until the end of the clinical trial.

The NBT used in this study is not a clinical investigational product and does not require allocation concealment, since it is administered to all groups. Moreover, it is impossible to blind the investigator and the participant in each group due to the nature of the study intervention, which is based on the contact between the patient and the medical staff. Instead, the investigator maintains blinding to prevent bias in evaluating the participant. After the clinical trial is completed, all clinical report forms (CRFs) will be collected, the database process terminated, and unblinding performed, if required for statistical analysis. Moreover, if it is deemed necessary to confirm the subject group due to an emergency situation during the clinical trial, the randomization code will be disclosed only to the participant, according to the principal investigator's discretion. If it is not possible to consult with the principal investigator and the situation is urgent, the randomization code of the subject will be disclosed after consultation with the randomization code officer. If unblinding is performed, the documentation of the reason for the unblinding will be retained, and the participant with the disclosed randomization code will not be able to continue the trial.

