**Efficacy evaluation**
In the efficacy evaluation, ITT will be treated as the main analysis group, and PP sets will be treated as the secondary analysis group. All statistical analysis will be conducted as two-sided tests with a significance level of 5%. Two-sided 95% confidence interval will be presented. Descriptive statistics will be presented for each treatment group and visit. Descriptive statistics and 95% confidence intervals will be presented for differences between the baseline and each visit.

Among efficacy evaluation variables, missing values of continuous variables will be analyzed using baseline observation carried forward correction.

A. Analysis of primary endpoints

For symptoms of lumbosacral radiculopathy at each measurement time point, descriptive statistics (number of patients, mean, and standard deviation) of the ODI score and changes in ODI at the end of treatment (4 weeks) and follow-up (8 weeks) compared with the baseline will be presented.

Paired *t*-test or Wilcoxon's signed ranked test will be conducted for intra-group changes in ODI at the end of treatment (week 4) compared with the baseline (0) depending on the satisfaction of normality. An analysis of variance model that includes changes in ODI at the end of treatment compared with the baseline as effects and baseline ODI as covariates will be used to evaluate the effects in the treatment group compared with the control group. Differences in least-square mean between treatment and control groups will be calculated, and two-sided 95% confidence interval and *P* value for the differences will be presented.

B. Analysis of secondary endpoint

Changes in ODI at follow-up (8 weeks) compared with baselineAssessment of subjective pain intensity in patients with lumbosacral radiculopathy-Lumbosacral radiculopathy pain will be divided into lower back and lower extremity pain using NRS, MPQ, and K-RMDQAssessment of quality of life related to lumbosacral radiculopathy-Evaluation of overall quality of life using EQ-5D. The same analysis methods for primary endpoints will be used to analyze secondary endpoints

C. Exploratory efficacy evaluation

Evaluation related to additional NBT or surgery after completion of the study

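### Patients dropped on discretionary or adherence grounds have no further ODI scheduled and are then scored at baseline; keeping them on the week-4 and week-8 ODI visits is a cheap improvement

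*Protocol article*

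**What the plan says.** **Grounds for dropout (section 2.8.7.1).** Item 1 bars "medications that are expected to affect the safety and effectiveness of NBT and acupotomy". Its third sub-item adds "Medications that may pose a risk to the patient or cause bias in the results as judged by the clinical investigator". Item 7 adds "Patients who are judged to be unfit to continue in the study for other reasons at the discretion of the clinical investigator". Items 5 and 6 drop patients for non-adherence: fewer than 6 of the 8 acupotomy sessions (combination arm only), or a single missed NBT (either arm).

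**Blinding (section 2.6).** The article states that "it is impossible to blind the investigator and the participant in each group", and then that "the investigator maintains blinding to prevent bias in evaluating the participant".

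**Outcomes after dropout (Table 1 and footnote #).** The row "Primary endpoint evaluation" is ticked at visits 1, 6, 11 and 12 and once in the drop-out column. After that, "For patients who dropped out of the study, exploratory evaluation is conducted after 4 weeks from dropping out". That evaluation asks only about further NBT or surgery, not ODI.

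**Missing values (section 2.9, Efficacy evaluation).** "missing values of continuous variables will be analyzed using baseline observation carried forward correction". The ITT set requires at least one follow-up after randomisation.

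**The concern.** The word joining the two halves of the third sub-item makes possible bias an alternative to patient risk, so it is a non-safety ground. Item 7 has no safety limit either. Section 2.6 protects outcome evaluation from knowledge of the arm, but nothing assigns the dropout decision to a blinded person.

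Dropout as defined here ends ODI collection as well as treatment, and the analysis then inserts the baseline value. A judgement made after randomisation can thus turn an obtainable primary outcome into zero change. The same happens under items 5 and 6, so the loss comes mainly from ending collection and scoring at baseline, not from the bias clause alone. Item 5 applies to one arm only, and the combination arm has 12 visits against 6, so unequal dropout is plausible.

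**Working it through.** **1. The plan's own figure.** Section 2.3 takes 20 per arm and 20% dropout: 20 / (1 - 0.20) = 25 per arm, 50 in total. This reproduces. The planned rate is 0.20 x 25 = 5 patients per arm, from all causes. The article gives no ODI mean, SD or power, so every such value below is an assumption.

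**2. What happens to a dropped patient under the stated rules.**
- No follow-up after randomisation: leaves the ITT set and is not scored at baseline.
- In the ITT set, dropped before week 4: zero change at weeks 4 and 8. The drop-out ODI is given no role in the efficacy rule. The economic analysis, by contrast, carries a withdrawn patient's last value forward.
- Dropped after week 4: the primary value stands and only week 8 is replaced.

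Item 6 acts before week 4, since the NBTs fall on days 7-8 and 21-22 and the week-4 ODI on days 26-28.

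**3. Unequal dropout, no true effect.** Assumptions: 25 per arm, ODI change with mean -12 and SD 12, baseline ODI with mean 40 and SD 12, correlation of baseline with change -0.3, change analysed on arm and baseline, two-sided 5%, 40,000 simulated trials. Without dropout the shift is 0.0 and type I error 4.9%. With random dropout of k of 25 in one arm, the expected shift is k/25 x 12; for k = 3 that is 1.44. If the dropout decision favours patients doing badly, the shift falls and then reverses. A positive shift means that the arm with dropouts looks worse.

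| Correlation of dropout decision with week-4 change (3 v 0) | Shift, points | Type I error |
|---|---|---|
| 0 | +1.43 | 6.7% |
| 0.3 | +0.76 | 5.0% |
| 0.5 | +0.29 | 4.5% |
| 0.7 | -0.17 | 4.6% |
| 1 | -0.83 | 5.6% |

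A second run of 15,000 trials agreed (6.9%, 4.5% and 5.5% at correlations 0, 0.7 and 1).

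Sensitivity:
- 1 v 0: shift -0.45 to +0.46, type I error 4.7 to 5.4%.
- 3 v 0 with mean -6 to -18, SD 8 to 16, correlation 0 to 0.7: shift -1.4 to +2.2, type I error 4 to 11%.
- 5 v 0 at random, SD 12, mean -10 to -20: shift +2.0 to +4.0, type I error 9 to 18%. This needs the whole planned dropout in one arm and none in the other.
- Extreme case (t-test, SD 15, mean change 0 to -10): the worst patients in one arm are identified perfectly and any worsening is reset to baseline. Type I error is 6 to 7% for one patient and 8 to 20% for five.

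**4. Equal dropout, true difference 10 points.** Random dropout scored at baseline multiplies the difference by 1 - k/25: 10 x 0.88 = 8.8 for 3 v 3, and 10 x 0.80 = 8.0 for 5 v 5.

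| Dropout | Power, scored at baseline | Power, observed values (none to all of the effect kept) |
|---|---|---|
| none | 85% | - |
| 3 v 3 | 71% | 74 to 85% |
| 5 v 5 | 60% | 65 to 84% |

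**5. What observed values cannot remove.** If 3 of 25 in one arm truly lost the whole -12 change after stopping, the observed shift would be 3/25 x 12 = +1.44, the same as with baseline scoring. That would be a real consequence of stopping, not an imputation artefact.

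**The case against.** **The bias clause is narrow.** It sits inside a prohibited-medication rule and needs a drug to trigger it; only item 7 is fully open. This stands, and it is why the point is about outcome collection after any dropout rather than about one phrase.

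**A reader might infer that the investigator can steer the result.** The documents do not support that. They give no count of discretionary dropouts. Section 2.6 uses the same word for the role that cannot be blinded and the role that is, and section 2.8.7.1 does not say which one decides. The direction of any shift is open.

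**A reader might charge the 20% dropout, and the fall in power from 85% to 60%, to items 1 and 7.** That rate covers all causes, including withdrawn consent, which no rule can recover. Section 2.3 also presents the trial as preliminary and claims no power.

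**A reader might infer that every dropped patient is scored at baseline.** The ITT definition rules this out for those with no follow-up.

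**The analysis plan, not shown, may say how the drop-out ODI is used.** That is fair, and its absence here is no finding. But the grounds, the visit schedule and the baseline rule are all fixed in this article, and no analysis plan can recover week-4 or week-8 values that were never collected.

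**Rescue drugs are already mostly covered.** Item 1 points to the rescue-medication section, so a further line on them would be largely editorial.

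**Conclusion.** The point holds as a cheap improvement. Followed as written, the plan replaces some obtainable ODI values with zero change after non-safety or adherence-based dropout. The likely effect is small and could go either way: about -0.8 to +1.4 points, with type I error of about 4.5 to 7%, for 3 v 0 dropouts under an assumed mean change of -12 and SD of 12. Equal dropout shrinks a true difference by the dropout fraction. Larger distortions need extreme imbalance or near-perfect selection. These simulations keep all 25 per arm, so they describe patients who stay in the ITT set and are dropped before week 4.

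A reader might conclude that collecting ODI after dropout removes all bias. It removes only the imputation distortion, and only for patients who are followed. If stopped patients keep none of the effect, the gain in power is small (71% to 74% for 3 v 3).

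**What to change.** - In section 2.8.7.1, for every dropout ground except withdrawal of consent, separate stopping study treatment from stopping outcome collection.
- In Table 1 and footnote #, keep these patients on the scheduled week-4 and week-8 ODI assessments. Section 2.2 allows telephone or online contact only after the treatment period, so it helps mainly at week 8; week 4 would normally be an attendance.
- In section 2.9, analyse the observed values in the ITT set and keep baseline carried forward only for values that are still missing.
- Delete possible bias in the results as a dropout ground, and record such medication as concomitant use or a protocol deviation.

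Safety-based stopping of treatment and the target of 50 patients do not change. The cost is a wording change and a few more patients attending visits already in the schedule. Dropped patients are already contacted once, 4 weeks after dropout.

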### Sample size calculation

2.3

This is a practical clinical study to assess the effects NBT and deeply inserted acupotomy combination treatment on lumbosacral radiculopathy.

In a previous pilot RCT that compared the therapeutic effects of deeply inserted acupotomy and general acupuncture in lumbar disc herniation patients,^[14]^ considering a 20% drop-out rate, a total of 50 patients (25 each in the acupuncture and deeply inserted acupotomy groups) were included.

In another RCT that compared the effects of deeply inserted acupotomy and general acupuncture in lumbar disc herniation patients,^[15]^ a total of 40 patients (20 each in the acupuncture and deeply inserted acupotomy groups) were included.

The phase 1 preliminary clinical study that will be conducted aims to estimate the mutual effects of NBT and deeply inserted acupotomy combination treatment and assess whether the combination treatment is effective and safe compared with conventional treatment. Thus, the study must be conducted with a minimum number of patients within the limit that satisfies the study purpose. Currently, there is no previous study that has provided the same intervention. Therefore, based on previous studies that provided similar treatment interventions and involved disease groups as in our study, 20 patients were included in each group. Considering a dropout rate of 20%, a total of 50 patients (25 patients in each group) was set as the target sample size.

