### Statistical analysis

2.9

For efficacy analysis, the intent-to-treat (ITT) group will be mainly analyzed, and secondary analysis will be done on the per-protocol (PP) group. Safety analysis will be performed on the ITT group patients who undergo at least one procedure after randomization. The ITT group will include all patients who have been randomly assigned, undergo at least one follow-up, and are eligible for efficacy assessment. PP group will include patients who satisfy the following conditions:

1.patients who satisfy both selection and exclusion criteria;2.those who have completed the pre-determined minimum number of acupotomy (6 out of 8 sessions); and3.those whose symptoms were improved and who satisfied treatment completion criteria

1.

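### Non-adherence and late-found ineligibility are made study dropout, so later scheduled ODI values go uncollected and are replaced by zero change in the main ITT analysis, unequally between arms

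*Protocol article*

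**What the plan says.** Section 2.8.7.1 (Dropout criteria) lists three items that concern adherence or eligibility rather than loss of contact. Item 4 covers serious violations, such as ineligibility, found during the study. Item 5 covers combination-arm patients who "have not conducted 6 or more of the 8 planned acupotomy treatments". Item 6 covers patients in either arm who "fail to conduct even one of the planned NBT". Items 5 and 6 spare anyone who meets the early-termination criteria. Section 2.8.7.2 ties those criteria to improved symptoms and counts such patients as compliant.

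Table 1 has a Drop-out column in which the primary and secondary endpoints are marked once. After that, the Table 1 footnote and section 2.8.3 describe one contact 4 weeks after dropout, by telephone if needed, about additional NBT or surgery. No later ODI is described for a dropout.

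Section 2.9 makes ITT the main efficacy set. It requires at least one follow-up and eligibility for efficacy assessment. Missing continuous efficacy values are filled by baseline observation carried forward (BOCF). The per-protocol set in the same section includes "those who have completed the pre-determined minimum number of acupotomy (6 out of 8 sessions".

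On sample size, section 2.3 states that "20 patients were included in each group" and then: "Considering a dropout rate of 20%, a total of 50 patients (25 patients in each group) was set as the target sample size".

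**The concern.** The same 6-of-8 threshold does two jobs. In the per-protocol definition it identifies adherent patients, which is a normal use. As a dropout criterion it also stops outcome collection. The patients who make ITT differ from per-protocol are then the ones without on-schedule outcomes, and the main analysis uses an assumed value for them although many could still be reached.

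Two features keep this loss from being neutral. Item 5 exists in one arm only. And two patients with the same missed sessions are classed differently according to whether symptoms improved: one counts as compliant, the other as a dropout.

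The sample size allowance does not distinguish rule-driven exits from true loss to follow-up, and item 6 has two readings that give very different numbers of exits.

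**Working it through.** **The plan's own figure.** 20 per arm with 20% dropout: 20/(1 − 0.20) = 25 per arm, 50 in total. This reproduces. The allowance is 5 of 25 per arm, 10 of 50 overall. The 20 rests on the size of earlier trials, with no effect size, SD or power behind it.

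**Inputs.** Eight acupotomy sessions and two NBTs (sections 2.4.1, 2.4.2). Item 5 is triggered by 3 or more of 8 missed. The documents give no adherence rate, so I assume each visit is missed independently with probability p and show a range. Item 4 is not in the calculation.

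**Formulas.**
- Item 5: a = P(Binomial(8, p) ≥ 3).
- Item 6, first reading (any one NBT missed): b = 1 − (1 − p)². Second reading (no NBT received): b = p².
- Control exits: b. Combination exits: 1 − (1 − a)(1 − b).

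At p = 0.10, a = 1 − 0.4305 − 0.3826 − 0.1488 = 0.0381. On the first reading b = 0.19, and the combination arm has 1 − 0.9619 × 0.81 = 0.221. On the second b = 0.01, and the combination arm has 1 − 0.9619 × 0.99 = 0.048.

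| p | a | First reading: combination / control | Second reading: combination / control |
|---|---|---|---|
| 0.05 | 0.006 | 10.3% / 9.8% | 0.8% / 0.25% |
| 0.10 | 0.038 | 22.1% / 19.0% | 4.8% / 1.0% |
| 0.15 | 0.105 | 35.4% / 27.8% | 12.5% / 2.3% |
| 0.20 | 0.203 | 49.0% / 36.0% | 23.5% / 4.0% |

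**Against the allowance.** On the first reading at p = 0.10, expected exits are 25 × 0.221 = 5.5 and 25 × 0.190 = 4.8, or 10.3 in total against 10 allowed. The chance of 5 or more exits is 0.68 in the combination arm and 0.53 in the control arm. Solving for 20% gives p = 9.2% (combination) and 10.6% (control) on the first reading, and 18.5% and 44.7% on the second.

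**When exits occur.** If exit comes at the third missed session, the chance that this is session k is C(k−1, 2) p³(1 − p)^(k−3). At p = 0.10 this is 15 × 0.001 × 0.6561 = 0.0098 for session 7 and 21 × 0.001 × 0.5905 = 0.0124 for session 8. Together that is 0.0222/0.0381 = 58% of item 5 exits, and session 8 alone is 33%. Table 1 puts these sessions on days 23–25 and 26–28, close to or at week 4. Item 6 on the first reading behaves differently. The first NBT falls on days 7–8, and at p = 0.10 a share of 0.10/0.19 = 53% of NBT-driven exits occur there, before the week 2 assessment.

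**Effect on the estimate.** Let d₁ and d₀ be the exit fractions in the combination and control arms, and E₁ and E₀ the true mean improvements of the exiting patients. BOCF scores them as zero. Ignoring baseline adjustment, using observed values instead changes the between-arm difference by d₁E₁ − d₀E₀. On the first reading at p = 0.10 this is 0.221E₁ − 0.190E₀, which is positive if E₁ exceeds 0.86E₀ and negative if it is below. The direction is not known in advance.

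**The case against.** The strongest reply is that the protocol already handles these patients. Those with at least one follow-up who are eligible for efficacy assessment stay in the ITT set with zero change. A reader might infer that the main analysis is therefore close to a per-protocol analysis. The documents do not support that: per-protocol removes these patients, while ITT keeps them as unimproved. The problem is imputed in place of observed values.

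A reader might also infer that week-4 ODI is never observed in non-adherent patients. That goes too far. Table 1 gives dropouts one ODI, and for most item 5 exits at p = 0.10 it would fall near week 4. What is reliably lost is week 8, which section 2.9 treats as secondary. Early NBT-driven exits do lose week 4.

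Nor is it shown that 20 analysable patients per arm would be lost, or that stated power would fail. BOCF keeps most such patients in the analysis, and no power was stated.

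The size of the loss depends on an assumed miss rate. At p = 0.05 even the harsher reading uses about half the allowance (2.6 + 2.4 = 5.0 of 10), with almost no difference between arms. Misses clustered in the same patients would lower NBT-driven exits further. On the second reading, exhausting the allowance in the control arm is implausible. All of this stands.

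That the article condenses protocol version 1.3 is not an answer, because the article itself states what happens after dropout.

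**Conclusion.** The concern holds in a limited form. Followed as written, items 4 to 6 turn non-adherence or a late-found violation into an end of outcome collection. BOCF then replaces the later scheduled ODI with zero change in the declared main analysis. Item 5 makes this unequal between arms, and the early-termination exemption ties dropout status to improvement.

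That the rule alone uses up the 20% allowance is conditional. It needs about 9–11% of visits missed on one reading of item 6, and about 18.5% (combination) and 45% (control) on the other. Both rest on independent misses at a rate the documents do not give. At p = 0.10, control-arm exits run from 1% to 19% depending only on how that one phrase is read, so the wording needs settling whatever the true adherence. The change is one that should be made.

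**What to change.** Reword items 4 to 6 so that they exclude a patient from the per-protocol set without ending outcome collection, and record non-adherence separately from withdrawal of consent. Keep consenting patients on the week 2, 4 and 8 assessments, timed from randomisation. Section 2.2 already allows telephone, survey or online assessment after the treatment period. Analyse the observed values in the assigned arm in place of BOCF. State which reading of item 6 is meant and make the related passages agree. None of this changes whether or how anyone is treated.

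The two rules would then cause no loss of outcome data. The sample size stays at 20/0.80 = 25 per arm, with all 5 places per arm left for true loss to follow-up. The cost is amendment wording and a few extra outcome contacts at time points already in the schedule. The estimated difference may move in either direction, because observed values replace imputed zeros.
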